#### Recruitment

Outpatients in clinics are the main recruitment targets. Posters and online publicity containing a brief introduction to the trial and the contact information of the researchers will also be used for recruitment. Before enrollment, each patient is provided with a complete and comprehensive description of the test procedure, its purpose, potential AEs, and expected benefits. Subjects are also informed that they may withdraw from the trial. If a patient agrees to participate in the trial, he/she will sign two informed consent forms, one kept by the patient and the other kept by the researcher. Subjects with involuntary or incomplete autonomy can also enter the trial after the consent of the ethics committee, and the informed consent form will be signed by their guardian.

### Allocation

#### Sequence generation and implementation

A central randomization system (CRS) is applied to ensure a completely randomized design. The randomized system mainly includes the following modules: subject screening, randomization, emergency unblinding, drug formulation, drug supply management, and other functional modules. The central randomization principle is as follows: The researcher uses the screening module to enter some basic information for the subject (such as date of birth, gender) and obtain the subject’s unique identification number (SIN). Firstly, the researcher confirms that the patient meets the inclusion criteria, logs into the CRS, inputs the general information for the subject, generates the random number, and fills in the eCRF. Secondly, drug distributors apply for the drug number from the CRS according to the random number. Finally, the drug senders verify the code on the drug package with the number in the system, and then the drugs are given to the patients.

#### Concealment mechanism

In this study, the CRS is used to centrally control the allocation of the entire randomization scheme. The “central randomization” method is used to conceal the allocation: When researchers determine that the subjects are qualified, the researchers log into the CRS, enter some basic information for the subjects, and obtain the subjects’ SIN. Then, the CRS will assign the subjects’ random numbers and drug numbers according to a designed blind table. In order to make the blind method effective and reduce drug loss, the random numbers are separated from the drug numbers in this system. Although the random number and the drug number are different, their corresponding treatment plans are consistent within the system.

#### Blinding and emergency unblinding

This is a double-blind trial. The blinding method is set up and implemented by the Medical Statistics Center of Tianjin University of Traditional Chinese Medicine. Neither the study researchers nor the subjects know the medication grouping. In the course of the trial, a scientific and strict management implementation system and feasible operation methods are used. All the subjects are put under a standardized observation with their clinical symptoms carefully recorded. Adverse reactions are carefully observed, and emergency unblinding is required for serious adverse reactions.

A regular supervision, inspection, and return system is used to ensure the implementation of the double-blinding method.

Unblinding will be performed at the end of the trial to perform a statistical analysis of all the data. The outcome assessment will be blinded. After all the research data have been entered and locked, the third party participants who saved the blinding codes and the researchers will jointly unblind and submit the database to the statistical analyst. When the entire statistical analysis is completed, statistical analysis and clinical trial summary reports will be written by the researchers.

#### Data collection plan and data management

The investigator will prepare original documents for each subject who was randomized into the study, and the information will be recorded in the CRF. All research results (personal data, test documents, etc.) that appear in the original medical records will be completely confidential within the scope allowed by law. Subject names will not appear in the CRF; only the name initials and the random number will be shown. The content should be comprehensive and accurate so as to record all examination results and other relevant data. The research center shall keep these documents properly for 5 years after the end of the research. The researcher will authorize the relevant regulatory agency to directly access all research-related documents.

There are principles for handling loss to follow-up: (1) if the loss is due to adverse reactions, the data will be recorded in the adverse reaction statistics; (2) if the loss is due to ineffectiveness, the data will be included in the efficacy statistics; (3) for those patients who were effective during the treatment but could not complete the entire course, and those lost to follow-up, these data will be included in the efficacy statistics and should be analyzed intentionally.

### Statistics

#### Outcomes

For the statistical analysis comparing the primary outcome incidence between the two groups, we will use the χ^2^ test and set *P* < 0.05 (95% confidence interval) as statistically significant. For the secondary outcomes, the measurement data are expressed as mean ± standard deviation, the count data are expressed as frequency and percentage (*f*, %), and the frequency or percentage of the efficacy evaluation index is converted into frequency and percentage (*f*, %). For comparison of the mean between the two groups, the homogeneity test is performed first. If the variances are equal, the *t* test is used. If the variances are unequal, the non-parametric *t* test is used. The measurement data of each group before and after treatment are compared using the paired *t* and/or *t* test. The comparison of grid table count data will be performed using the χ^2^ test, and the comparison of rank data will use the rank sum test. *P* < 0.05 will be used as the statistical difference. The data analysis will be performed using SPSS 19.0 statistical software.

The baseline is defined as the last observation data before the first medication, which includes demographic characteristics and clinical baseline data: age, sex, vital signs (height, weight, temperature, heart rate, blood pressure, breathing), clinical symptom scores, HBV DNA, liver stiffness (FibroScan/Fibrotouch), entecavir treatment history, and CHB-related diseases.

#### Additional analyses

There are currently no plans to do subgroup analyses or sensitivity analyses.

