#### Sample size

The aim of this study is to reduce the annual incidence of cirrhosis from 2% ~ 10% [30] to 1% in patients with CHB. Therefore, according to the sample size estimation formula for comparison of two sample rates, the incidence of target events is less than 0.2 (or 0.3) or greater than 0.8 (or 0.7), shown as follows:
$$ \mathrm{n}=\frac{{\left({u}_{\alpha }+{u}_{\beta}\right)}^2}{2{\left({\mathit{\sin}}^{\hbox{-} 1}\sqrt{p_e}{\hbox{-} \mathit{\sin}}^{\hbox{-} 1}\sqrt{p_c}\right)}^2} $$

Here *p*_*e*_ and *p*_*c*_ represent the incidence rates of the test group (YQSH group) and placebo group (control group), respectively. The positive event rate (*p*_*c*_) in the control group is 5%, while the target event rate (*p*_*e*_) in the test group is set to 1%. Since the values of p_e_ and p_c_ are small, the degree is measured in radians, α = 0.05, and β = 0.10. In this study, a two-sided test was chosen, *u*_0.05_ = 1.96, *u*_0.10_ = 1.282, *p*_*e*_ = 0.05, *p*_*c*_ = 0.01. The calculated sample size of each group is approximately 334 cases. Therefore, allowing for 20% attrition, the total number of patients required for this trial is 334*(1 + 20%)*2 = 802 cases, with 401 in each group.

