#### Analysis population and missing data

We will use three methods for statistical analysis of the data:
Full analysis set (FAS). According to the intention-to-treat (ITT) principle, all randomized subjects’ data will enter the FAS. For subjects who withdraw from the study early for various reasons, the missing data will be imputed using the method of last observation carried forward (LOCF).Per protocol set (PPS). The study’s PPS will consist of the indicator data for those who enter the study and complete treatment and follow-up, whose medication compliance is 80–120%, who took no combined medication that affected the effectiveness evaluation during the study period, and who have complete evaluation index data and no major test protocol violations.Safety set (SS). The SS includes those subjects who received at least one treatment after randomization.

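### No sensitivity analysis is planned for missing cirrhosis status, although expected losses (134 to 160) far exceed expected events (about 19 to 24) and LOCF counts early losses as cirrhosis-free

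*Protocol article*

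**What the plan says.** All references are to the protocol article.

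- **Additional analyses:** "There are currently no plans to do subgroup analyses or sensitivity analyses". This is a stated choice, not silence.
- **Analysis population and missing data:** the full analysis set holds all randomised patients, and for those who withdraw early "the missing data will be imputed using the method of last observation carried forward (LOCF"). No other rule for missing data is given. The same section defines a per-protocol set of patients who finish treatment and follow-up, meet a compliance range, take no interfering medication, and "who have complete evaluation index data and no major test protocol violations".
- **Exclusion criteria and Primary outcome:** patients with cirrhosis are excluded at entry. The primary outcome is read before treatment, at week 52 of treatment, and at the 52-week follow-up visit.
- **Sample size:** "The calculated sample size of each group is approximately 334 cases", then "allowing for 20% attrition, the total number of patients required for this trial is" "802 cases, with 401 in each group". The assumed rates are 5% (placebo) and 1% (YQSH).
- **Modifications, and Data collection plan and data management:** the listed reasons for discontinuation or loss include deterioration, complications, unresolved liver-function abnormality, ineffectiveness and adverse reactions.

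**The concern.** The primary endpoint is rare and binary, and the plan expects several times more lost patients than events. In that setting the rule for missing cirrhosis status can carry much of the result. For anyone lost before week 52 the only reading to carry forward is the baseline one, which is cirrhosis-free by eligibility. LOCF therefore fixes the answer for those patients whatever happened to them.

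Several of the listed reasons for leaving the trial bear on prognosis, so loss related to outcome is plausible. Whether it would differ by arm is unknown. Nothing planned would show a reader how far a significant difference depends on that. This is separate from whether LOCF is a good main rule: replacing it with another single rule and leaving the Additional analyses statement in place would leave the same gap.

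**Working it through.** **Inputs.** From Sample size: 401 per arm (802 in total), 334 evaluable per arm, 20% attrition, event rates 5% and 1%, cited control range 2% to 10%, two-sided α = 0.05. From Statistics: a χ² test for the primary outcome. No continuity correction is mentioned, so none is applied below.

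**1. The plan's own figure.** n = (1.96 + 1.282)² / [2(arcsin√0.01 − arcsin√0.05)²] = 10.511 / (2 × 0.12535²) = 334.5 per group. Then 334 × 1.2 × 2 = 801.6, rounded to 802. The figure reproduces.

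**2. Expected losses.** There are two readings:
- 20% of those randomised: 0.20 × 802 = 160, or about 80 per arm, leaving 321 per arm.
- Randomised minus evaluable: 802 − 2 × 334 = 134, or 67 per arm.

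**3. Expected events at 5% v 1%.**
- 321 per arm: 321 × 0.06 = 19.3
- 334 per arm: 334 × 0.06 = 20.0
- 401 per arm: 401 × 0.06 = 24.1

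**4. Losses per event.** Highest 160.4 / 19.3 = 8.3; lowest 134 / 24.1 = 5.6. Over the cited control range the ratio runs from 16.7 (160.4 lost; 321 × 0.03 = 9.6 events) down to 3.0 (134 lost; 401 × 0.11 = 44.1 events). Losses exceed events on every reading.

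**5. What hidden cases do to the test.** With 80 lost per arm, expected observed events are 0.05 × 321 = 16 and 0.01 × 321 = 3. If all 80 are lost before week 52, LOCF analyses 16 v 3 of 401. Uncorrected Pearson χ², 401 per arm:

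| Assumption about the 80 missing per arm | Placebo v YQSH events | p |
|---|---|---|
| No cases in either arm (LOCF) | 16 v 3 | 0.0025 |
| 5% in both arms (4 and 4) | 20 v 7 | 0.011 |
| 0 placebo, 3 YQSH | 16 v 6 | 0.031 |
| 0 placebo, 4 YQSH (5%) | 16 v 7 | 0.057 |
| 4 placebo, 6 YQSH (7.5%) | 20 v 9 | 0.037 |
| 4 placebo, 7 YQSH (8.8%) | 20 v 10 | 0.063 |

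**6. The other attrition reading.** With 67 lost per arm, observed events are about 17 v 3 (p = 0.0015). Four unseen YQSH cases and no placebo cases give 17 v 7, p = 0.038; five give 17 v 8, p = 0.067.

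**7. Smaller positive results (401 per arm, no unseen placebo cases).**
- 12 v 3, p = 0.019: one unseen YQSH case gives p = 0.043, two give p = 0.086.
- 13 v 4, p = 0.027: one unseen YQSH case gives p = 0.057.

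**8. What the per-protocol set would show.** Dropping the lost patients gives 16 v 3 of 321, p = 0.0025, the same as under LOCF. At equal loss the two agree whatever happened to those who left.

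**9. Reference-based imputation at the planned effect.** Missing patients in both arms are drawn at the placebo completers' rate (16/321, about 5%) and combined by Rubin's rules. The risk difference is about 0.032 with standard error 0.0144, so p is about 0.025.

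**The case against.** The strongest reply has five parts.

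- **The per-protocol set is a check of a kind.** It imputes nothing, so readers would see one result with LOCF and one without. This stands, and it defeats the inference that the missing-data assumption goes wholly unexamined. But that set leaves the lost patients out and also selects on compliance and concomitant medication. It is not presented as a test of outcome-related loss and cannot serve as one (step 8).
- **The loss of significance needs a lopsided scenario.** This also stands. Equal 5% rates give p = 0.011 and reference-based imputation about 0.025. With 5% among missing placebo patients, the YQSH rate among the missing must reach 8.8%, above the plan's own control rate.
- **The attrition reading matters.** With 67 lost per arm, the same four unseen cases leave p = 0.038. True, although a fifth gives p = 0.067.
- **Not every lost patient goes unexamined.** Someone lost in the second year has a real week-52 reading, which LOCF carries forward. The document gives no split by time of loss, so 80 per arm never assessed is an upper bound under that reading.
- **The wording is provisional and the article is condensed.** An unseen analysis plan might add such analyses. But the article addresses the topic and says none is planned, so this is a stated position and not a detail left elsewhere.

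A reader might infer that a positive result could not be defended at all. The document does not support that: at the planned effect the result survives equal missing rates and reference-based imputation. The small-effect examples also start near 0.05, so part of their fragility comes simply from rare events.

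**Conclusion.** The point holds in a limited form. The plan declines sensitivity analyses while expecting 5.6 to 8.3 losses per event at its own design rates, and its one imputation rule counts early losses as event-free. The per-protocol analysis is a partial check that does not address loss related to outcome and differing by arm.

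At the planned effect the conclusion is fairly robust to similar missing rates in the two arms but not to differential loss: four unseen YQSH cases among 80 missing, with none in placebo, move p from 0.0025 to 0.057. More modest positive results turn on one or two unseen cases.

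These figures assume an uncorrected χ² test, events at exactly the planned rates, 80 lost per arm and all losses before week 52. Fewer or later losses would soften them. The document gives no evidence that loss will in fact differ by arm. The primary test remains valid as a calculation; what is missing is a pre-specified view of how far it depends on unobserved patients. This should be changed, at little cost.

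**What to change.** In Additional analyses, remove the reference to sensitivity analyses and keep the decision on subgroups. Pre-specify for the primary outcome, before unblinding:

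1. A tipping-point table giving the χ² p value for each combination of cirrhosis cases among missing YQSH and missing placebo patients, with the boundary at which significance is lost.
2. A reference-based multiple imputation in which missing patients take the placebo completers' rate.

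State that both are reported beside the primary result, with numbers lost before and after week 52 by arm, so that patients with a real week-52 reading are told apart from those with none.

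The cost is a paragraph of text and a little programming on data already collected, with no added patients or visits. The downside is that a positive result may have to be described as fragile; equally, the table could show that it is robust.

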#### Analysis population and missing data

We will use three methods for statistical analysis of the data:
Full analysis set (FAS). According to the intention-to-treat (ITT) principle, all randomized subjects’ data will enter the FAS. For subjects who withdraw from the study early for various reasons, the missing data will be imputed using the method of last observation carried forward (LOCF).Per protocol set (PPS). The study’s PPS will consist of the indicator data for those who enter the study and complete treatment and follow-up, whose medication compliance is 80–120%, who took no combined medication that affected the effectiveness evaluation during the study period, and who have complete evaluation index data and no major test protocol violations.Safety set (SS). The SS includes those subjects who received at least one treatment after randomization.

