#### Exclusion criteria

The exclusion criteria are as follows: (1) patients with cirrhosis; (2) patients with liver cancer; (3) patients in acute and chronic hepatitis with non-HBV infection, autoimmune hepatitis, primary biliary cirrhosis, primary sclerosis cholangitis, inherited metabolic liver disease, drug or toxic hepatitis, or alcoholic liver disease; (4) pregnant or lactating women or women planning to become pregnant during the study period; (5) patients who are allergic to the test drugs; (6) patients who have mental disorders and cannot cooperate with the study, or patients with epilepsy in unstable status; (7) patients with severe systemic disease related to the heart, brain, lung, kidney, or hematopoiesis; (8) patients with alcoholism or other unsuitable conditions for enrollment. Patients who are already using TCM will not be enrolled unless they have stopped using TCM for more than 3 months.

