#### Modifications

If a patient shows abnormal liver function (such as ALT > 2*ULN) during the trial, this should prompt temporary or permanent cessation of treatment, and the investigator can add hepatoprotective drugs such as silibinin and/or other drugs according to the patient’s condition. At the same time, the researchers will record and follow up the situation of the patient closely. If the patient’s ALT returns to normal after liver protection treatment, with normal values for direct bilirubin and international normalized ratio (INR) at the same time, then he/she may have a chance to continue the trial; otherwise, the patient will stop the trial permanently for safety reasons. If the following conditions occur, subjects should discontinue the trial: (1) poor compliance, irregularly taking medicine, failure to revisit or revisit on time; (2) some combined diseases or complications, or deterioration during the trial; (3) subject self-withdrawal; (4) combining trial drug with other drugs, or not taking test drugs according to research regulations; (5) lost contact; (6) cannot provide complete information.

We also list the following specific stopping criteria. (1) Serious safety problems occur during the test; then the test should be stopped in a timely manner. (2) The drug is found to have no clinical value during the trial; then the trial should be stopped to avoid delaying the effective treatment of subjects. (3) It is found during the trial that there is a major error in the clinical trial protocol and it is difficult to evaluate the effect of the drug; or there is a well-designed protocol with important deviations in the implementation, and it is difficult to continue to evaluate the efficacy and safety of the drug. (4) The sponsor requests to stop the trial (for funding reasons, management reasons, etc.). (5) The State Food and Drug Administration of China orders the trial to be stopped for some reason. (6) The test is suspended due to *force majeure* reasons.

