### Outcomes

#### Primary outcome

The primary outcome is the annual incidence of cirrhosis (the examination methods include instantaneous liver elastic hardness test, abdominal B-mode ultrasound test, or abdominal MRI/CT imaging).

The primary outcome is evaluated before the treatment, at 52 weeks of treatment, and at the 52 ± 2 weeks follow-up visit.

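### LOCF on the cirrhosis outcome counts patients who leave before week 52 without an unscheduled diagnosis as cirrhosis-free, and no sensitivity analysis is planned to test this

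*Protocol article*

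**What the plan says.** Four statements in the protocol article combine.

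- **Eligibility** (Exclusion criteria): "The exclusion criteria are as follows: (1) patients with cirrhosis". Every randomised patient should start without the event.
- **Outcome and timing** (Primary outcome): "The primary outcome is the annual incidence of cirrhosis", and "The primary outcome is evaluated before the treatment, at 52 weeks of treatment, and at the 52 ± 2 weeks follow-up visit". The Secondary outcomes section adds visits at week 26 of treatment and of follow-up, but for the secondary outcomes only.
- **Missing data** (Analysis population and missing data): "all randomized subjects’ data will enter the FAS", and for those who withdraw early "the missing data will be imputed using the method of last observation carried forward (LOCF"). No separate rule is given for the primary outcome.
- **Sensitivity** (Additional analyses): "There are currently no plans to do subgroup analyses or sensitivity analyses".

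Two further places bear on who goes missing. Among the reasons to discontinue the trial, the Modifications section lists "some combined diseases or complications, or deterioration during the trial". It also provides for a permanent stop when abnormal liver function does not resolve. The data management section puts losses due to ineffectiveness into the efficacy statistics but does not say that they count as events.

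**The concern.** LOCF assumes that a patient's status stays where it was last seen. For an incidence outcome in patients free of the event at entry, that is the best possible result, assigned without uncertainty. With no scheduled assessment between baseline and week 52, the rule does not use partial information on cirrhosis. For these patients it simply records a non-event.

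Two things are at stake. The recorded incidence is too low in both arms. If the arms lose different proportions of patients before week 52, the arm that loses more looks better for that reason alone. Because some reasons for leaving concern worsening disease, the patients counted as event-free may be those at higher risk. Few events are expected (5% and 1% of 401 are about 20 and 4), so a handful of misclassified patients matters.

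**Working it through.** **Inputs.** From the Sample size section: 5% in the placebo arm, 1% in the YQSH arm, two-sided α = 0.05, β = 0.10, 20% attrition, 401 per arm. From Statistics, Outcomes: χ² test. The timing of loss, any imbalance in loss and the relative risk in leavers are not in the document and are assumed below.

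**The plan's own figure.** n = (1.96 + 1.282)² / [2(asin√0.05 − asin√0.01)²] = 334.5, stated as 334; 334 × 1.2 × 2 = 801.6, stated as 802. It reproduces.

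**How many patients.** 0.20 × 802 ≈ 160, if all loss falls before week 52. If half falls later, about 80, because later leavers have an observed week-52 status.

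**Recorded rates.** Let d be the proportion lost before week 52, p the true overall risk in an arm, and m the risk in leavers relative to stayers. The stayers' risk is s = p / (1 − d + m·d), and LOCF records s(1 − d).

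- d = 0.20, m = 1: 0.05 × 0.8 = 4.0% and 0.01 × 0.8 = 0.8%.
- d = 0.20, m = 3: 0.05/1.4 × 0.8 = 2.86% and 0.01/1.4 × 0.8 = 0.57%.

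**Power at a true 5% v 1%**, by exact binomial enumeration of the uncorrected χ² test. LOCF uses 401 per arm; observed cases use 321 per arm (401 × 0.8).

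| Scenario | LOCF | Observed cases |
|---|---|---|
| 20% loss per arm, m = 1 | 87.8% | 88.6% |
| 20% loss per arm, m = 3 | 72.8% | 75.2% |

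Full follow-up of 401 per arm would give 94.2%. Most of the drop from there is attrition. LOCF itself adds 0.8 points at m = 1 and 2.4 points at m = 3.

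**Rejection rate with no true effect (5% in both arms)**, same method. Loss is YQSH v placebo.

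| Loss before week 52 | m | Recorded under LOCF (YQSH v placebo) | Rejection, LOCF | Rejection, observed cases |
|---|---|---|---|---|
| 20% v 20% | 1 | 4.0% v 4.0% | 4.8% | – |
| 25% v 15% | 1 | 3.75% v 4.25% | 6.3% | – |
| 25% v 15% | 3 | 2.50% v 3.27% | 9.8% | 6.1% |
| 30% v 10% | 1 | 3.5% v 4.5% | 10.8% | – |
| 30% v 10% | 3 | 2.19% v 3.75% | 25.5% | 9.9% |

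In the last row, 25.4 of the 25.5 points favour YQSH. The worked line for 25% v 15% with m = 3 is 0.05/1.5 × 0.75 = 2.50% and 0.05/1.3 × 0.85 = 3.27%.

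**The case against.** **Power.** A reader might set 87.8% against 94.2% and blame LOCF for the gap. That does not stand. No analysis recovers full follow-up, and against observed cases the cost is small. Power is not the reason to change the rule.

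**Number affected.** A reader might take 160 of 802 as settled. The article gives 20% attrition without timing, and the trial runs a further 52 ± 2 weeks after treatment. The figure is an upper bound.

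**False positives.** A reader might conclude that the plan carries a false-positive rate of 10% or 25%. Those rates need 30% v 10% loss in a double-blind, placebo-controlled trial, and nothing in the document suggests such an imbalance. Part of the 25.5% is informative dropout that observed cases would share (9.9%). More loss on placebo would work against YQSH. With equal loss and equal risk, the rejection rate stays near 5%.

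**Wording.** The article reports no current plans for sensitivity analyses, which does not forbid them. The per-protocol set contains no carried-forward outcomes, but it keeps only compliant completers with complete data, so it cannot test the assumption. Cirrhosis found at an unscheduled examination could be carried forward as an event, and the schedule figure is not available here. Some patients with raised ALT may resume, so not all of them leave.

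What survives is the mechanism. Three explicit statements together assign a favourable outcome to these early leavers, and no planned analysis examines that. This is a stated rule, not detail left to an analysis plan.

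**Conclusion.** The point holds as a badly chosen missing-data rule for the primary outcome. Patients who leave before week 52 without an unscheduled diagnosis are recorded as cirrhosis-free with certainty, although some reasons for leaving plausibly relate to the outcome.

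The effect on incidence is direct: 4.0% v 0.8% instead of 5% v 1% if 20% of each arm leaves before week 52 at the same risk as those who stay. The effect on the comparison depends on imbalance. For a moderate one (25% v 15%), false rejection rises to 6.3%, or 9.8% with threefold risk in leavers, where observed cases would give 6.1%. The direction follows whichever arm loses more. The document does not support a claim that the trial is biased towards YQSH or that power is materially lost through LOCF.

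**What to change.** In the missing-data section, drop LOCF for the primary outcome. State that every cirrhosis assessment actually obtained, in all randomised patients, enters the analysis. Handle missing status by multiple imputation with a small model, for example arm, baseline liver stiffness and entecavir treatment history, all of which are collected. With about 16 and 3 events expected among those observed at 20% loss (401 × 4.0% and 401 × 0.8%), a larger model would be unstable.

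Replace the sentence under Additional analyses with a pre-specified tipping-point analysis that varies the assumed cirrhosis risk among missing patients separately by arm. This is more useful than a single worst case, which with up to 80 missing per arm would swamp the observed events.

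The cost is analysis wording and programming, and slightly wider intervals. The article describes no cirrhosis assessment after a patient discontinues the trial. Collecting one would be extra follow-up with its own cost, and this fix does not depend on it.

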**Methods:**

This is a multicenter, randomized, placebo-controlled, double-blinded trial involving five hospitals. A total of 802 patients are randomly allocated to two groups: the YQSH group (*n* = 401) or the placebo group (*n* = 401). The YQSH group receives YQSH with entecavir; the placebo group receives granules of placebo with entecavir. Patients receive treatment for 52 weeks and then are followed up for 52 ± 2 weeks. The primary outcome measure is the annual incidence of cirrhosis. The secondary outcome measures are hepatitis B virus DNA negative rate, hepatitis B surface antigen negative rate, hepatitis B e antigen seroconversion rate, liver function (alanine aminotransferase, aspartate aminotransferase , gamma-glutamyl transferase , alkaline phosphatase , serum albumin, and total bilirubin), spleen thickness, evaluation scores of patients’ clinical symptoms, and safety assessment. Outcomes will be assessed at baseline and after treatment.

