#### Secondary outcomes

The secondary outcomes include HBV DNA negative rate, HBsAg negative rate, HBeAg seroconversion rate, liver function (ALT, aspartate aminotransferase [AST], gamma-glutamyl transferase [GGT], alkaline phosphatase [ALP], serum albumin [ALB], and total bilirubin [TBIL]), spleen thickness, and the evaluation scores of patients’ clinical symptoms.

These indicators are observed before the treatment, at 26 weeks of treatment, at 52 weeks of treatment, at the 26 ± 2 weeks follow-up period, and at the 52 ± 2 weeks follow-up period.

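### LOCF without exception carries earlier values of the secondary outcomes into the two post-treatment visits and tests them as if observed; the bias is of unknown size and direction, and nothing planned would reveal it

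*Protocol article*

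**What the plan says.** The Analysis population and missing data section sets an intention-to-treat population: "all randomized subjects’ data will enter the FAS". It then fixes one imputation rule for subjects who withdraw early: "the missing data will be imputed using the method of last observation carried forward (LOCF". The rule is not limited to the primary outcome or to particular visits.

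The Secondary outcomes section lists virological rates, six liver tests, spleen thickness and symptom scores. After baseline they are read "at 26 weeks of treatment, at 52 weeks of treatment, at the 26 ± 2 weeks follow-up period, and at the 52 ± 2 weeks follow-up period". The Abstract places follow-up after treatment: "Patients receive treatment for 52 weeks and then are followed up for 52 ± 2 weeks".

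Three other sections bear on the point:

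- Modifications ties exit to liver tests. A subject with abnormal liver function may resume if ALT, direct bilirubin and INR are normal after liver-protective treatment; "otherwise, the patient will stop the trial permanently for safety reasons".
- Data collection plan and data management keeps subjects who did well but stopped early, and those lost to follow-up, in the efficacy statistics.
- Additional analyses plans no sensitivity analyses.

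**The concern.** The follow-up visits can show whether an effect seen on treatment lasts. LOCF answers that question for early leavers by assuming that nothing changed after their last reading. Their treatment-period values are then reported as results from up to a year after treatment ended.

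Three things follow.

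- Follow-up rates and means are pulled towards earlier values.
- If dropout differs between arms, that pull differs too and can create or hide an arm difference.
- The t and χ² tests named under Statistics would treat the filled-in values as data.

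Exit is also not unrelated to the outcomes. ALT is a secondary outcome and can trigger permanent exit, while subjects with a good response who stop early are kept. So LOCF may hold poor values for some leavers and good values for others.

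This is separate from what LOCF does to the primary outcome, where the value carried may be a non-cirrhotic baseline. Here intermediate readings exist and can inform a model.

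**Working it through.** **1. Does the rule reach the follow-up visits?** The missing-data section covers every randomised subject and excepts no outcome. The secondary-outcome schedule has four post-baseline visits, two of them after week 52. Read together, a subject who leaves during treatment has an earlier value entered at both follow-up visits. No single sentence says so, but it follows from the two sections.

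**2. How many subjects could this touch?** The only attrition figure is in Sample size. The plan's formula gives (1.96 + 1.282)² / [2(asin√0.01 − asin√0.05)²] = 334.5 per group, stated as about 334. Then 334 × 1.2 × 2 = 801.6, stated as 802, or 401 per group. The figure reproduces and is used here only for scale. At the planned attrition, between 401 − 334 = 67 and 0.20 × 401 = 80 subjects per arm could carry an earlier value at the last visit. The protocol does not say when they leave, and those who leave during follow-up could carry a follow-up value instead.

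**3. Effect on a reported rate.** Let d be the proportion leaving during treatment, T the carried on-treatment rate and F the true follow-up rate, taken as the same for leavers and stayers.

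- Reported rate = (1 − d)F + dT, so bias = d(T − F).
- Assumptions, none from the document: T = 80%, F = 60% or 40%. The 20% for d borrows the attrition allowance.
- F = 60%: 0.8 × 0.60 + 0.2 × 0.80 = 64%, 4 points too high.
- F = 40%: 0.8 × 0.40 + 0.2 × 0.80 = 48%, 8 points too high.
- T = F: bias is zero.

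**4. Effect on the comparison when there is no true difference.** The spurious difference is (d₂ − d₁)(T − F). The rejection probability uses a two-sided 5% test by normal approximation, with 401 per arm and null standard error √[2p̄(1 − p̄)/401].

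| Dropout | F | Reported rates | Difference | z | Rejection |
|---|---|---|---|---|---|
| 20% v 20% | 60% | 64% v 64% | 0 | 0 | 5% |
| 20% v 20% | 40% | 48% v 48% | 0 | 0 | 5% |
| 15% v 25% | 60% | 63% v 65% | 2 points | 0.02/0.0339 = 0.59 | about 9% |
| 15% v 25% | 40% | 46% v 50% | 4 points | 0.04/0.0353 = 1.13 | about 21% |

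**5. Range.** With T = 90% and F = 80%, 60% or 40%, dropout of 15% v 25% gives differences of 1, 3 or 5 points and rejection of 6.6%, 14.6% or 29.3%. An extreme split of 10% v 30% gives 2, 6 or 10 points and 11.4%, 43.4% or 81.0%.

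**6. Would counting a missing result as not achieved be safer?** The same null case with 15% v 25% dropout:

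- F = 60%: 0.85 × 0.60 = 51% v 0.75 × 0.60 = 45%, about 40% rejection, against about 9% for LOCF.
- F = 40%: 0.85 × 0.40 = 34% v 0.75 × 0.40 = 30%, about 23% rejection, against about 21% for LOCF.

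It is much worse in one case and no better in the other.

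**7. Would anything planned expose the problem?** The per-protocol set requires completed treatment and follow-up and complete evaluation data. It is free of LOCF only because it drops the subjects in question, so it cannot test the assumption made about them.

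**The case against.** The strongest objection is that the size rests on assumptions. The illustration has the HBV DNA negative rate falling from 80% to 60% or 40% after treatment. The protocol does not say whether entecavir stops at week 52, and it admits patients already taking it. If entecavir continues, the shift between phases, and so the bias, could be small. The unequal dropout is also assumed: the plan gives one 20% allowance, and the trial is double-blind with entecavir in both arms. Both points stand.

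Two stronger readings are tempting and are not supported.

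- A reader might infer that a raised ALT recorded at exit is frozen and counted at every later visit. The protocol describes no exit visit, does not say whether an unscheduled value counts as the last observation, and says such patients will be followed closely. Only the last available observation can be said to be carried.
- A reader might infer that LOCF inflates the false-positive rate in general. With equal dropout and no true effect it does not in this calculation; only the reported rates are wrong.

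It can also be said that these are secondary outcomes, that a statistical analysis plan may refine the method, and that the per-protocol analysis is a partial check. The first limits the weight of the point. The second does not remove it, because the article states a method rather than leaving it open. The third fails for the reason in step 7.

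**Conclusion.** The point holds in a limited form. As written, the plan enters earlier values of the secondary outcomes as results at the two follow-up visits and tests them as observed, in a trial where exit can depend on one of those outcomes and no planned analysis checks the assumption.

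The size and direction of the bias are unknown. Direction may differ by outcome and by reason for leaving. Under the main assumed rates with 20% dropout, follow-up rates are overstated by 4 to 8 points. A false arm difference of 2 to 4 points needs unequal dropout as well. The primary outcome is not part of this point. It should be changed, but it does not threaten the trial's main conclusion.

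**What to change.** Replace LOCF for the secondary outcomes in the Analysis population and missing data section.

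- **Liver tests (log scale where skewed), spleen thickness, symptom scores:** one repeated-measures mixed model per outcome on observed data, with arm, visit, arm-by-visit and baseline value. Read the arm difference at each visit from it.
- **HBV DNA, HBsAg and HBeAg rates:** multiple imputation by arm from the earlier visits.
- **Reporting:** give the number actually observed at each visit, by arm.
- **LOCF or missing-as-not-achieved:** at most a labelled sensitivity analysis, since step 6 shows that the second is itself biased when dropout differs. Amend Additional analyses to match.

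Both main methods still assume that the recorded earlier values account for who is missing; the plan should say so.

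The cost is revised wording and modest programming, with no new data. Intervals will be somewhat wider because filled-in values no longer count as observations.
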